## Abstract

**Background:**

Lack of exercise is often a major cause of chronic disease. Osteoporosis (OP) is a chronic disease with multifactorial co-morbidity. Baduanjin (BDJ) exercise may be a powerful tool for modifying risk factors. The aim is to provide more evidence about the effectiveness of BDJ exercise in improving pain and balance ability in patients with OP.

**Methods:**

In the prospective randomized controlled trial, 160 participants will be recruited and randomized to the treatment group (BDJ exercise combined with Calcium carbonate and D3) or the control group (Calcium carbonate and D3) at 1:1 ratio. Participants in the treatment group will receive 24-week BDJ exercise for 30–60 min, 3 times a week, along with Calcium carbonate and D3 at each day, while participants in the control group will receive Calcium carbonate and D3 only. All outcome indicators will be measured at baseline, after the 6th month of treatment and 6th month after the end of treatment. The primary outcomes include pain and balance ability, as measured by the visual analogue scale (VAS) and Berg balance scale (BBS). The secondary outcomes will primarily include bone mineral density (BMD), laboratory tests (including P1NP, β-CTX, MSTN, FDF-23, NPY), the timed “up and go” (TUG) test, the morse fall scale (MFS), the five-times sit-to-stand test (FTSST).

**Discussion:**

The study will hopefully confirm that BDJ exercise, as a non-drug intervention, should be recommended for patients with OP to prevent bone loss, falls and fractures.

**Trial registration:**

International standard randomized controlled trial number (ISRCTN) registry: ISRCTN76945140 registered on 07/06/2022.

## Background

Osteoporosis (OP) is a physiologically degenerative disease that occurs with age, often accompanied by a decrease in bone strength and an increased risk of low-energy or fragility fractures [1, 2]. The global prevalence of OP in the elderly was 21.7%, and the prevalence rates in Asia, America, and Europe were 24.3%, 11.5%, and 16.7%, respectively, with the highest in Asia [3]. According to a recent epidemiological survey about OP in China, the prevalence rate of men over 40 years old was 5%, and that of women over 40 years old was 20.6% [4]. Obviously, the situation is heavily serious, which poses a great challenge. OP, as a multifactorial co-causative chronic disease, has diverse approaches to prevention and treatment.

Lack of exercise is often the main cause of chronic diseases [5], and various forms of exercise have also become a sharp edge in fighting against diseases, which can be well balanced in both disease prevention and treatment [6]. At the same time, exercise is considered the most effective management method to improve physical function and mental health in the elderly, and widely recommended to improve bone health [7, 8]. In addition, various guidelines also suggest that a multi-component exercise program should be explored with OP, including resistance training, balance exercises, and aerobic physical activity [9–11]. Traditional Chinese exercises have been inherited and reformed, which combines the concepts of multicomponent movements, and play a significant role in combating the occurrence and development of diseases.

Baduanjin (BDJ), defined as an energy-burning exercise with traditional Chinese medicine characteristics, may be a powerful tool for adjusting risk factors about OP. This is a safe combination of aerobic and resistance exercise, consisting of eight movements that are less physically and cognitively demanding, easier to learn and practice, less restrictive and safe [12]. Therefore, BDJ exercise is a very suitable choice for the elderly because it can enhance body function by coordinating posture, movements, breathing and meditation throughout the body. Previous series studies have shown that BDJ exercise can provide physiological benefits, including improving cardiovascular risk factors [13, 14], quality of life [15], and mental health [16]. In China, BDJ exercise has become a popular, safe, and health-promoting form among the elderly.

Bone mineral density (BMD) is the gold standard for OP, however, one of the characteristics of OP is pain and the serious outcome is fracture, and then, balance ability is closely related to the occurrence of fracture [9]. Therefore, the study focused on pain and balance ability, two key factors associated with the development of OP. At first, we conducted a systematic review and meta-analysis in order to initially explore the therapeutic effect of BDJ exercise on OP [17], and the results suggested that it might be beneficial to improve BMD, relieve pain, improve balance ability, influence serum bone gla protein (BGP) and alkaline phosphatase (ALP) in patients with OP, and we also found previous studies to be of low quality. Therefore, we will plan to conduct a prospective superior randomized controlled trial and further determine the effectiveness of BDJ exercise on pain and balance improvement, which can provide a broad perspective in relationship between BDJ and OP.

## Methods

### Study aim and design

The protocol design is a two-arm parallel randomized controlled trial with allocation concealment and blinding of the assessors. Participants or the public were not involved in the design, or conduct, or reporting, or dissemination plans of our research. The procedure and outcome evaluation schedule for this trial are shown in Figs. 1 and 2.

**Fig. 1 Fig1:**
[figure not shown]
Flow diagram of the study

**Fig. 2 Fig2:**
[figure not shown]
Outcome evaluation schedule

### Study population

The participants are OP patients, with no gender restriction. The diagnostic, inclusion, exclusion, and withdrawal criteria are as follows.Diagnostic criteriaReferring to the *Chinese Guidelines for the Diagnosis and Treatment of Primary Osteoporosis* (2022) [18] and WHO [19], the diagnosis is mainly based on the BMD of dual energy X-ray absorptiometry (DXA). Based on DXA results, the study will select T-value ≤ -2.5 as the subject screening criterion. DXA will be operated by trained imaging technicians assigned by each sub-center.Inclusion criteriaEligible participants meet the following criteria: 1) Primary OP: T-value ≤ -2.5. 2) Female aged from 45 to 70 years old and menopause time is greater than 2 years, which are met at the same time. Male aged from 50 to 70 years old. 3) Visual analogue scale (VAS) is greater than or equal to 3 points. 4) Patients who are willing to participate in the study.Exclusion criteriaThe exclusion criteria are as follows: 1) Lumbar fusion or severe degeneration hinders BMD measurement, and there are less than two continuous intact lumbar vertebrae that can be evaluated by DXA. 2) Patients with serious primary diseases, such as cerebrovascular, digestive tract, and lung diseases, because these clinical manifestations may interfere with the results of the study. 3) Secondary OP: abnormal bone mass caused by similar diseases, including diabetes, thyroid disease, Cushing's syndrome, rheumatoid arthritis, multiple myeloma, gout, malabsorption syndrome, systemic lupus erythematosus, etc. 4) The participants have taken drugs that affect bone metabolism within 3 months before enrollment, such as bisphosphonates, glucocorticoids, calcitonin, anticonvulsant drugs, heparin, etc. 5) Those with a history of severe mental illness or poor compliance. 6) Allergic constitution. 7) Those who have participated in other clinical trials within 3 months.Withdrawal criteria and managementParticipants will be allowed or required to withdraw for the following reasons: 1) Violation of the protocol. 2) Severe illness that prevents continuation. 3) Serious adverse events during the study period. 4) Voluntarily asked to withdraw from the trial. 5) Lost to follow-up. 6) Using drugs that may affect bone metabolism during the period.

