### Randomization

Participants who meet the inclusion and exclusion criteria will be randomly divided into the control group and the treatment group, with 80 patients in each group. Due to the peculiarities of BDJ exercise itself, we could not blind participants or trainers, but outcome assessors and statisticians will be blind. The research will entrust a professional data management department to generate random numbers system (http://112.126.58.121:8082/bdj) and monitor trial quality. According to the group designated by the random number, research assistants accurately record the participants' random number, group, and intervention.

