### Intervention

During the trial period, participants in the treatment group will be given BDJ exercise combined with Calcium carbonate and D3, and in the control group will be only given Calcium carbonate and D3. The intervention period will last 24 weeks. The requirements for the BDJ exercise will be as follows.Preparatory stage (the first 2 weeks, mastering movements stage)Participants need to be organized to practice BDJ exercise for 3 times a week. The researchers will hire professional coaches to guide and correct the movements. During rest time, research assistants will distribute free videos to practice by themselves at home.Conventional stage (the last 22 weeks, regular exercise stage)The participants need to exercise 3 times a week, 30 to 60 min each time, and the amount of exercise may be appropriate as long as the participants do not experience fatigue. The research assistants will lead exercise once a month, and the rest time will be practiced by themselves. The researchers will give monthly follow-up calls or home visits to record the completion and adjust the exercise frequency according to the actual conditions. During the trial period, the researchers will instruct the participants to avoid other physical activities as much as possible, for example, swimming. If there are associated exercises, the research assistant needs to record details.We will recommend the participants form a small team to exercise together with their familiar people, and distribute free brochures, BDJ exercise teaching videos and special lectures about OP at different periods, so as to maximize enthusiasm and compliance, which can ensure the study completion to the greatest extent.

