### Sample size

According to the existing results combined with expert experience [21, 22], we assume α = 0.05 and β = 0.10 based on an allocation ratio of 1:1, then the sample size is 64 cases respectively in the two groups, totaling 128 cases according to VAS. Considering the 20% dropout rate, a total sample size of 160 cases is required. Then, we also calculated the sample size to be 146 cases according to BBS. Finally, we set the sample size of this study to 160 cases.

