### Statistical analysis

All statistical analyses were performed using SPSS 25.0 and Python 3.11. Statistical significance was set at a P value less than 0.05. Continuous variables that conform to a normal distribution are represented by the mean and standard deviation, and variables that do not conform to a normal distribution are represented by the median and interquartile range. Categorical variables will be described as frequencies or percentages. Missing data will be filled in using multiple imputation.

To account for correlation among repeated measurements, intervention effects on the primary and secondary outcomes were examined by generalized estimating equations (GEE) with baseline measurement as the covariates. The group-by-time interaction, which indicated the difference for a given outcome between interventions over time, was considered our primary measure of intervention effects.

Adverse effects will be analyzed using the χ^2^ test or Fisher's test. If it cannot run a normal analysis, we will choose descriptive analysis for presentation.

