## Discussion

As an integrated mind–body exercise, BDJ is less physically and cognitively demanding than Tai Chi. A recent meta-analyses suggested that mind–body exercise might be the best exercise type to increase BMD in the lumbar spine and femoral neck [23]. Exercise causes gravitational and muscle-contractional loads on the bones, and lack of exercise is often the main cause of bone loss in weight-bearing bones [5]. Therefore, the stress stimulation of BDJ exercise on the bones determines that it could be an effective treatment for OP.

The biggest challenge is compliance in this study. Even more frightening are concerns about adherence to OP treatment, compared with the consequences of low bone mass. It is estimated that more than 70% of individuals at risk of OP who are on treatment do not receive continue treatment beyond the first year [24]. Active exercise is far more effective than passive therapy. Exercise training is more effective than actual therapist therapy in reducing pain, improving physical function, and mental health [25]. It is far from enough to passively promote their awareness only by external intervention, and every elder person needs to pay more attention. Patient’s adherence about exercise programs is known to be a difficult area in clinical practice. Many patients do not follow clinician recommendations and are at risk of worsening their condition [3]. We are also actively preparing for this issue, for example, we encourage community residents who are familiar with each other, which is also convenient for us to manage. At the same time, we will establish an online communication group and organize community lectures to deal with such situations.

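### The withdrawal list does not separate stopping the intervention from leaving follow-up, so avoidable missing outcomes would be left to an unstated missing-at-random assumption

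*Protocol article*

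**What the plan says.** Study population (withdrawal criteria) gives one list of six reasons for which a participant may, or must, withdraw. It opens with "1) Violation of the protocol" and closes with "6) Using drugs that may affect bone metabolism during the period". Between them stand severe illness, serious adverse events, a participant's own request to leave the trial, and loss to follow-up. The list does not say which reasons compel withdrawal and which only permit it, or whether outcome assessment continues afterwards.

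Statistical analysis states: "Missing data will be filled in using multiple imputation". It also says that "intervention effects on the primary and secondary outcomes were examined by generalized estimating equations (GEE) with baseline measurement as the covariates", with the group-by-time interaction as the main measure of effect.

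Three other places bear on the point:
- **Intervention:** only the treatment arm has an exercise schedule, while participants "in the control group will be only given Calcium carbonate and D3". Staff may adjust exercise frequency, and other exercise is to be recorded.
- **Safety measurements:** there is a separate rule for stopping the exercise when complications or adverse reactions occur.
- **Discussion:** "The biggest challenge is compliance in this study".

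**The concern.** Protocol violation, serious adverse events and starting a bone-active drug all arise after randomisation. Each can be related to the allocated arm and to pain or balance. If they lead to exit from the trial, the missing outcomes are created by the rule itself, and imputation has to supply values that could have been measured.

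Standard multiple imputation assumes that, given the observed data, withdrawn participants resemble those retained in their arm. For someone removed because they did not exercise, that assumption is doubtful. BDJ has the more demanding protocol, three sessions a week for 24 weeks and mostly unsupervised in the last 22. The authors themselves expect trouble with compliance. Because "we could not blind participants or trainers, but outcome assessors and statisticians will be blind", a decision to require withdrawal can be made in knowledge of the arm.

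At stake is whether the reported effect applies to everyone randomised to BDJ or mainly to those who kept it up. The trial is meant to support a clinical recommendation, which needs the former.

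**Working it through.** **1. Reading the list.** Loss to follow-up and a request to leave the trial are exits from the trial. Protocol violation, serious adverse events and bone-drug use stand in the same list under the same verb. Safety measurements uses different language when only the exercise is to stop. Trial exit is therefore the most natural reading of the list, though it is not stated.

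**2. The plan's own figure.** Sample size gives 64 per arm for the VAS and 20% dropout: 128 / (1 − 0.20) = 160, which reproduces. Exits that the rule itself causes draw on that same allowance. No VAS difference or SD is printed. The article says "we assume α = 0.05 and β = 0.10 based on an allocation ratio of 1:1". Taking α as two-sided (an assumption), 64 per arm implies a standardised difference d = (1.960 + 1.282) × √(2/64) = 0.573. A one-sided α would imply 0.517. I use 0.573 only as an example; the percentages in step 3 do not depend on it.

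**3. Non-adherers removed from the BDJ arm.** Assumptions: a share p of the BDJ arm is withdrawn for non-adherence, they keep a fraction f of the benefit, and imputation fills them in from the retained BDJ participants.

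- Effect in all randomised = d × (1 − p + p·f)
- Effect targeted after imputation = d
- Overstatement = 1 / (1 − p(1 − f)) − 1

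| p | All-randomised effect, f = 0 | Overstated by | All-randomised effect, f = 0.5 | Overstated by |
|---|---|---|---|---|
| 5% | 0.544 | 5% | 0.559 | 3% |
| 10% | 0.516 | 11% | 0.544 | 5% |
| 20% | 0.458 | 25% | 0.516 | 11% |
| 30% | 0.401 | 43% | 0.487 | 18% |

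**4. No true effect.** Now let violators be s SD worse than the rest for prognostic reasons, with violators removed from the BDJ arm only. The bias towards BDJ is p·s. A simulation (4,000 runs, 80 per arm, available-case difference as a stand-in for imputation) gave these chances of a false result favouring BDJ, against a nominal 2.5%:

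| p | s | Bias p·s (SD) | False result favouring BDJ |
|---|---|---|---|
| 20% | 0 | 0 | 2.7% |
| 10% | 0.5 | 0.05 | 4.8% |
| 20% | 0.5 | 0.10 | 9.0% |
| 20% | 1.0 | 0.20 | 20% |

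The first row shows no inflation beyond simulation error. The simulation ran neither the planned GEE nor a baseline-adjusted imputation. Adjustment would remove whatever part of s the baseline values predict.

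**5. Bone-drug starters in the control arm.** Let q be the share starting, g the drug's benefit, and s how much worse starters are than the rest. The bias towards BDJ is q × (g − s). Over q = 5–20%, g = 0–0.6 SD and s = 0–1 SD it runs from 0.20 × (0 − 1) = −0.20 SD to 0.20 × (0.6 − 0) = +0.12 SD. For starters in the BDJ arm the sign reverses. The direction is not fixed.

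The values of p, f, q, g and s are all assumed. The article gives no withdrawal rate by arm or reason.

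**The case against.** The strongest reply is that the article does not describe removing non-adherers. Intervention has staff record completion and adapt exercise frequency, keeps the amount of exercise flexible, and only logs other exercise. The Discussion answers poor compliance with encouragement, an online group and lectures. Nowhere is low adherence defined as a violation. This stands, and it makes step 3 conditional. It does not remove the problem, because the withdrawal list still puts protocol violation first and does not say what counts as one.

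Second, imputation after withdrawal is an inference from joining two sections; the article does not say that assessments cease. That also stands. Post-withdrawal visits, analysis sets and imputation details may be set out in a full protocol or SAP not shown, and their absence here is no finding. The point rests on a rule that is printed and, on its natural reading, ends measurement. A later analysis plan cannot recover outcomes that were never collected.

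Third, controls have a calcium and D3 regimen that they too can violate, and all six reasons apply to both arms. So unequal removal is plausible but not established.

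A reader might also infer that the randomised comparison is broken. It is not: multiple imputation keeps each person in the allocated arm, and what changes is that validity depends on the missing-data assumption.

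**Conclusion.** The concern holds in a limited form. As worded, the list most naturally turns several post-randomisation events into trial exit, and the one stated remedy relies on a missing-at-random assumption that those events make doubtful.

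If BDJ non-adherers are removed and gain less than those retained, the effect is overstated by 5% to 11% at 10% withdrawn and by 11% to 25% at 20% withdrawn. The lower figure in each pair is for half the benefit kept, the upper for none. These are illustrations, not forecasts.

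Two stronger readings are not supported:
- **That the rule as a whole favours BDJ.** For bone-drug starters the bias can go either way. With no true effect, removing violators who do not differ in prognosis causes no inflation.
- **That the effect will be overstated by 25%.** That figure treats the 20% dropout allowance, which covers both arms and all reasons, as if it were entirely BDJ non-adherence with no benefit at all.

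The uncertain size and direction are themselves reasons to measure these participants.

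**What to change.** Reword the withdrawal criteria so that protocol violation, severe illness, serious adverse events and use of bone-active drugs do not by themselves end outcome follow-up. Participants who still consent are measured at the planned 6- and 12-month visits and analysed in the arm to which they were randomised. Only withdrawn consent or true loss ends follow-up.

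In Statistical analysis, limit multiple imputation to values that could not be obtained, and add one sensitivity analysis that imputes missing BDJ outcomes from the control arm.

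Reconcile the withdrawal list with Intervention (handling of adherence) and Safety measurements (stopping the exercise), so that the three sections agree on what is a violation, what stops the exercise and what ends measurement. This concerns measurement and analysis only; it changes no clinical rule on exercise or drugs.

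The cost is protocol wording plus visits, already in the schedule, for participants who have stopped the intervention. The estimated effect may also be smaller.

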### Recruitment

Participants will be recruited from hospitals or communities in Beijing, Tianjin, and Shaanxi province, China. The recruitment form is mainly a combination of online and offline methods, including Internet publicity, and setting up on-site recruitment stations, etc. First, potentially eligible individuals will complete doctors screening to determine their eligibility based on inclusion and exclusion criteria. Qualified individuals interested in participating in the study will have an informed discussion with trained research assistants. Research assistants will obtain Informed Consent before starting the baseline assessment.

### Randomization

Participants who meet the inclusion and exclusion criteria will be randomly divided into the control group and the treatment group, with 80 patients in each group. Due to the peculiarities of BDJ exercise itself, we could not blind participants or trainers, but outcome assessors and statisticians will be blind. The research will entrust a professional data management department to generate random numbers system (http://112.126.58.121:8082/bdj) and monitor trial quality. According to the group designated by the random number, research assistants accurately record the participants' random number, group, and intervention.

